#### Policy reforms

The Swedish parental leave system has undergone several reforms over the past half-century. We define a ‘policy reform’ as any change implemented at a specific time that could impact either uptake or sharing of parental leave, as well as eligibility for earnings based benefits. To evaluate the unforeseen health consequences of the parental leave policy—that is, a welfare policy that does not primarily target health—we will concentrate on reforms that have either been shown to accomplish their primary aim (ie, the speed premium, father’s quota and double days reforms) or with undoubtedly significant, although unintended, impacts (ie, the doubled value of general flat-rate benefits).

Doubled flat-rate benefits: Although not explicitly a reform, the doubling of the general flat-rate benefits from 60 SEK per day (from 1987) to 120 SEK per day (in 2002) aimed to secure the economic welfare of low-income families.

Speed premium: Since earnings related parental leave benefits are estimated based on one’s salary prior to childbearing (at approximately 80% of the salary), parents having children in quick succession may choose to temporarily reduce their working hours or be unable to return to work at all and will thus have lower benefits for their second and subsequent births. In 1980, a supplement (commonly referred to as the ‘speed premium’) was introduced to safeguard women’s income between parental leave periods, ensuring that for births with up to 24 months’ spacing^13^ and then with up to 30 months’ spacing (following a 1986 expansion),^14^ all earnings based benefits could be based on the parents’ salaries prior to the birth of their previous child, if higher than their current income. An evaluation of the 1986 expansion revealed that an increased proportion of Swedish-born parents had children in short succession; even if this was an unintended consequence, the reform has henceforth been called the ‘speed premium’.^14^

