### Unintended health consequences of the Swedish parental leave system

Despite the relative generosity of the Swedish parental leave system and its efforts to promote gender equity, some aspects could be responsible for the maintenance or increase in social and health inequities. For example, the strong work-eligibility requirement for earnings based parental leave benefits may exclude groups with less stability in the labour market, such as students and migrants, from benefits equal to those enjoyed by persons with stable incomes.^17^

Inequities in the work-eligibility requirement can emerge in various ways, either by restricting the parental leave benefits scheme to the securely employed and coincidentally excluding parents with ill health (ie, health selection) or by creating health inequities through the unequal distribution of benefits (ie, social causation). For example, individuals with long-term illness may be more likely to have a weak labour market attachment, which in turn can exclude them from earnings related parental leave benefits, thus further increasing socioeconomic inequities. Based on this, we expect that the doubled flat-rate benefits could increase leave uptake among lower-income families or decrease the economic trade-off of using parental leave among lower-income families, thus having potential psychosocial benefits.

Parental leave policies might impact health differently following certain policy reforms. For example, the speed premium supplement introduced to secure earnings based parental leave benefits to parents who have children in quick succession essentially incentivises short birth spacing.^14^ This might lead to increased psychosocial stress and adverse reproductive outcomes among women who become pregnant while simultaneously rearing an infant or toddler. The WHO recommends a minimum of 24 months, assuming 9 months of gestation, before a new conception to avoid adverse reproductive outcomes.^18^ Short birth intervals have been associated with nutrition depletion,^19^ as the mother might not have enough time between births to recover her nutritional reserves and higher risks of weight gain and obesity throughout life.^20^ In turn, these issues are risk factors for adverse outcomes in subsequent children, including low birth weight, preterm birth and perinatal death.^18 21^

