### Aim/objectives and research questions (RQ)

The aim of this project is to evaluate the consequences of parental leave policy in Sweden from a health equity perspective. More specifically, the project will cover the following RQ:

RQ#1: Is eligibility for earnings based parental leave benefits associated with parents’ mental health?

RQ#2: Is short birth spacing in relation to the speed premium supplement reform associated with health problems in the subsequent pregnancy of the mother (early pregnancy obesity) and the subsequent child (low birth weight, preterm and small-for-gestational age)?

RQ#3: Does the introduction and expansion of the father’s quota reserve days influence the mental health of parents after the birth of their child?

RQ#4: Does the introduction of simultaneous parental leave use through the double days reform influence parents’ mental health?

RQ#5: Does the introduction of the father’s quota and double days reforms influence children’s health (episodes of respiratory tract infections, childhood obesity) or health-related outcomes (duration of breast feeding)?

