### Study design and statistical analyses

A variety of advanced designs and statistical methods for observational data will be applied. First, using descriptive and correlational designs, we will implement standard multivariable methods to quantify links between prebirth health conditions, parental leave eligibility and uptake, and postbirth health outcomes while accounting for confounding using relevant covariates and heterogeneity analyses.

Second, we will use robust quasi-experimental approaches to assess the causal effects of parental leave policy on health, reducing the risk of selection effects and unmeasured confounding by harnessing the natural, ‘as-if’ randomisation around policies.^45 46^ With this approach, we can isolate the absolute policy effects on health even in the absence of detailed information on changes in parental leave uptake. These approaches include interrupted time series (ITS), regression discontinuity (RD) and difference-in-difference (DiD) designs. For ITS designs, segmented regression models will be adjusted for seasonality and trend while accounting for autocorrelation.^46^ For RD designs, continuity around the cut-off will be tested using the McCrary Density Test and similarity of eligible and ineligible observations will be determined through descriptive statistics. Finally, for DiD designs, we will examine the data to confirm parallel trends and other relevant assumptions.^45^

RQ#1: We will examine the effects of the 2002 doubling of flat-rate benefits on the mental health of parents. An RD design will be applied to plot psychiatric hospitalisation rates with labour income as a forcing variable, with separate plots before (with an income cut-off equivalent to 75 SEK, at 80% reimbursement rate) and after 2002 (with a cut-off equivalent to 150 SEK daily). Cut-offs for both parents’ income will be examined. We will triangulate our findings with a DiD approach, comparing those eligible for the increased benefits to those ineligible before and after reforms.

RQ#2: A segmented-regression ITS of monthly birth data comparing the rate of low birth weight and preterm births 3 years before and after the 1980 and 1986 speed premium reforms will be implemented. We will also compare the prevalence of obesity in mothers early in their second pregnancy before and after the reform.

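### RQ#2 asks about short birth spacing, but its analysis never measures the interval between births, so it estimates the effect of each reform and not a spacing effect

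*Protocol article*

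**What the plan says.** In the Protocol article, under Aim/objectives and research questions, RQ#2 asks: "Is short birth spacing in relation to the speed premium supplement reform associated with health problems in the subsequent pregnancy of the mother" and in the subsequent child.

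Under Study design and statistical analyses, the child outcomes are handled by "A segmented-regression ITS of monthly birth data comparing the rate of low birth weight and preterm births 3 years before and after" the two reforms. For the mother, "We will also compare the prevalence of obesity in mothers early in their second pregnancy before and after the reform".

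Under Policy reforms, the 1980 supplement is described as "ensuring that for births with up to 24 months" of spacing, benefits could rest on the salary before the previous birth. The 1986 expansion raised that limit to 30 months. The same section reports the response to 1986: "An evaluation of the 1986 expansion revealed that an increased proportion of Swedish-born parents had children in short succession".

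The section on unintended health consequences builds the harm hypothesis on short intervals and gives a benchmark: "The WHO recommends a minimum of 24 months, assuming 9 months of gestation, before a new conception to avoid adverse reproductive outcomes".

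The interval between births is not listed under Outcomes, Covariates, Study design and statistical analyses, or Additional analyses. The subgroups named are income, education, nativity, age at childbirth and cohabitation.

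**The concern.** The question and the analysis have different exposures. The question is about spacing; the analysis compares outcome rates by calendar time. The step between them, that the reform shortened intervals in these data and that shorter intervals moved the outcomes, is left unmeasured. Yet the protocol reads this reform through spacing, both in the harm hypothesis and in the Limitations.

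At stake is the interpretation of whatever the regression shows. A change in preterm or low birth weight rates at either date could come through spacing. It could also come through a change in who has further children, or through younger maternal age at later births; the Limitations section names both of these. A finding of no change would be equally hard to read. The two dates also set different incentives, since 1980 introduced a limit and 1986 moved an existing one.

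**Working it through.** The protocol gives no sample size, effect size or power figure for RQ#2, so there is no figure to reproduce. The check has four steps.

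**1. Exposure in the question against exposure in the analysis.** The question's exposure is short birth spacing. The analysis compares birth months before and after 1 January 1980 and 1 January 1986. With three years on each side, the windows are 1977–1979 against 1980–1982, and 1983–1985 against 1986–1988. No interval variable enters as exposure, outcome, first-stage check or covariate.

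**2. The limits on one scale.** Using the 9 months of gestation in the cited recommendation:
- 24 months birth to birth leaves 24 − 9 = 15 months to conception.
- 30 months birth to birth leaves 30 − 9 = 21 months to conception.
- The recommended 24 months to conception is 24 + 9 = 33 months birth to birth.

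Both premium limits are therefore short by the protocol's own benchmark.

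**3. What the 1986 step could combine.** The 1983–1985 pre-period already lies under the 24-month rule. Moving the limit to 30 months gives parents who would have waited longer than 30 months a reason to shorten. It also lets parents who had kept within 24 months wait up to 30 − 24 = 6 months more without losing the premium. Let A be intervals of 24 months or less, B over 24 to 30, and C over 30. Let s be the share of births moving from C to B, l the share moving from A to B, and r the outcome risk in each class. Then

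change = s(rB − rC) + l(rB − rA).

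All values below are assumptions. With risks A 6.0%, B 5.0%, C 4.5%:
- s = 5%, l = 0: 0.05 × 0.005 = +0.25 per 1000
- s = 5%, l = 2%: 0.25 − 0.02 × 0.010 × 1000 = 0.25 − 0.20 = +0.05 per 1000
- s = 5%, l = 5%: 0.25 − 0.50 = −0.25 per 1000
- s = 2%, l = 5%: 0.10 − 0.50 = −0.40 per 1000

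Two other assumed risk sets (5.5/5.0/4.8% and 7.0/5.0/4.5%), with the same four pairs of shares, widen the range to −0.90 to +0.25 per 1000. The low end is 0.02 × 0.005 − 0.05 × 0.020 = −0.0009. In every case shorter spacing is harmful and more births fall within 30 months, yet the sign of the net change is not fixed. This shows what is possible, not what happened.

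**4. Which births are in the series.** RQ#2 concerns the subsequent child, but the analysis sentence speaks only of monthly birth data. First births have no preceding interval. If they stayed in, a change confined to later births would shrink in proportion. With an assumed 55% second or later births, +0.25 becomes 0.25 × 0.55 = +0.14 per 1000.

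**The case against.** The strongest reply is that interrupted time series estimates a policy effect, and the protocol says so: it describes its quasi-experimental designs as isolating policy effects even without detailed uptake data. RQ#2 also ties spacing to the reform. This stands. The planned regression is a valid reduced-form analysis, and a reader who inferred that it is invalid, or tells us nothing relevant to RQ#2, would go too far. What fails is only the reading as a spacing effect.

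Second, the protocol cites a first stage for 1986. That also stands, and it makes a 1986 result due to no change in spacing unlikely among Swedish-born parents. As described, however, it covers that group and that reform, and gives no split at 24 and 30 months. Nothing comparable is cited for 1980.

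Third, no text says that anyone lengthened an interval after 1986. That is correct: the route is inferred from the two limits. A move from 24 to 30 months also leaves the share of births under the 33-month benchmark unchanged, so it matters only if risk differs within the short range. A reader might infer that opposite shifts cancelled in 1986; the documents do not support that.

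Fourth, a reader might suppose that the two reforms will be pooled. The text does not say so.

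Fifth, the protocol plans analyses by nativity for RQ#2 and comparisons of population composition around each reform, and it acknowledges a possible benefit through younger maternal age. These help interpretation, but none of them measures spacing.

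**Conclusion.** The mismatch is in the text and does not depend on any assumed number: the question names spacing, and the analysis uses calendar time alone. Followed as written, the plan yields one reduced-form effect per reform, which cannot be attributed to spacing without further evidence. For 1986, the cited evaluation supports a net rise in short-succession births among Swedish-born parents, and the step should be read as a net effect of widening the limit. For 1980, no spacing response is documented. The size of any distortion cannot be derived from the documents, and the ranges above rest wholly on assumed shares and risks. That a derived interval is missing from a condensed covariate list would not be a finding on its own; the point rests on the stated question and the stated analysis having different exposures. It is a matter that should be put right, and it does not make the analysis unusable.

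**What to change.** 1. Restrict the low birth weight and preterm series to second (or second and later) births, and say so.
2. For each reform separately, add a first-stage interrupted time series of birth spacing, using sibling birth dates from the linked family registers, in three classes: 24 months or less, over 24 to 30, and over 30.
3. Handle left truncation. The medical birth register and the first-birth study population both start in 1973. For a second birth in January 1977, only intervals up to about 4 × 12 = 48 months are visible; by January 1982 it is about 9 × 12 = 108 months. Left alone, the over-30 class would grow artificially across the 1980 window. Either follow first-birth cohorts forward, or cap intervals at a length observable throughout 1977–1982.
4. Describe the health result as a policy effect. Call it consistent with a spacing pathway only where the interval series shifts toward shorter spacing and the checks of composition and maternal age do not explain it. A shift in spacing alone is not enough.
5. Do not stratify or restrict the health series by interval, because the reform itself may change the interval.

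The minimum alternative is to reword RQ#2 as a question about the effect of the reforms.

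The cost is one derived variable with care over its data source, a few more monthly series, and a narrower claim.

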Father’s quota: Fathers have been eligible to use parental leave since 1974, when parents could choose to divide parental leave days between themselves as they saw fit. However, most days were transferred to and claimed by mothers, with an average use of 320 days in 1994, reinforcing mothers’ ‘double burden’ of childcare and work. In response, a father’s quota reform was implemented in 1995, reserving a month of leave exclusively for the father, to be forfeited completely if left unused (similarly, a 30-day reserve was allocated to the mother, ie, a mother’s quota). It succeeded in increasing the proportion of fathers using parental leave from 43% to 75%.^15^ The father's quota was expanded to 2 and 3 months in 2002 and 2016, respectively, but with smaller impacts on uptake.^6^

Double days: In 2012, 30 days of existing parental leave were designated as ‘shareable’, that is, could be used simultaneously by both parents within the child’s first year of life. By granting flexibility to the couple in their leave use, this ‘double days’ reform aimed to facilitate the transfer of care from one parent to another. In fact, the reform significantly increased the proportion and number of father’s leave days used in the first half-year after childbirth.^16^

All reforms were implemented nationally on 1 January of the indicated year.

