### Outcomes

Child health outcomes include low birth weight (<2500 g, irrespective of gestational age), preterm birth (<37 gestational weeks) and a small-for-gestational age measure (<10th percentile of birth weight for each gestational age, based on sex-specific Swedish reference curve for normal foetal growth)^41^ from the MBR; hospitalisation episodes of respiratory tract infections during the first 2 years of life (International Classification of Diseases-10 (ICD-10) Codes J20.5, J21.0, J21.9, J20.9, J18.9, J12.9 and J22.9) from the NPR and duration of partial or exclusive breast feeding (at months 2, 4, 6, 9 and 12) as well as childhood obesity (body mass index (BMI); weight in kilograms/height in meters^2^ using age-specific and sex-specific cut-offs for children’s overweight and obesity^42 43^ at 18 months and 3–5 years) from the CHR. Maternal health outcomes include maternal early pregnancy overweight (BMI 25–29.9 kg/m^2^) and obesity (BMI 30–39.9 kg/m^2^).^44^

Mental health outcomes will be assessed for both parents using count data on purchases of prescription anxiolytic and antidepressant medications (Anatomical Therapeutic Classification Codes N05B and N06A, respectively) as well as outpatient visits and hospitalisations with a primary diagnosis of mental and behavioural disorders (until 1997, ICD-9 Codes 290–319; thereafter, ICD-10 Codes F00-F99), from childbirth to 18 and 36 months after birth.

Outcomes will be expressed as prevalence or rates, given availability of follow-up time.

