### Limitations

Despite our reliance on a robust quasi-experimental approach, it is difficult to predict the relative timing of the behavioural response to each parental leave reform (ie, in uptake) and its health consequences. Parents have been shown to respond quickly to policy changes,^14 15 27^ but given that some parents may not be aware of their eligibility on the reform dates, delayed reaction times could lead to lagged health effects for subgroups such as migrants.^12^ Thus, we will use a long follow-up both within the life course (ie, years since birth) and in the context of the policy (ie, years since reform implemented).

Quasi-experimental designs have the potential to reduce unmeasured confounding, but policies themselves, as well as ongoing trends, could inadvertently modify the composition of the study populations, potentially biasing any causal interpretations. For one, the speed premium may have affected the composition of individuals who decided to have children after the reform, that is, encouraging more parents eligible for earnings based benefits to have children after 1986, given their increased level of benefits for subsequent children. Exogenous impacts other than the policy under investigation could also contribute to changing population compositions, as in the case of the 1990s economic crisis, which may have discouraged couples with lower socioeconomic position from having children after the 1995 father’s quota. We will thus examine varying sociodemographic characteristics of the study populations before and after each reform to assess the robustness of the design to approximate causal effects, with corresponding subgroup and sensitivity analyses.

Registers generally have greater coverage than other data sources but may be prone to bias in the form of missing data and overcoverage (ie, unreported outmigration), which we will address in appropriate sensitivity analyses. The historical availability of register data may also influence our analytical choices. For example, to evaluate the impact of the father’s quota on psychiatric health, we will primarily look at the first reserved month introduced in 1995.^6^ However, only severe health outcomes (psychiatric hospitalisations) can be assessed with the available registers at that time. In order to evaluate less severe outcomes (outpatient visit and prescription data) of increased fathers’ leave use, we will evaluate the more recent double days reform.^16^

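### RQ#2 speed-premium series: if conceptions rise, a preterm rate indexed by month of birth shifts slightly with no change in risk; indexing by conception month removes this

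*Protocol article*

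**What the plan says.** Under Study design and statistical analyses, RQ#2 covers the speed premium reforms (1980 and 1986) and is described as "A segmented-regression ITS of monthly birth data comparing the rate of low birth weight and preterm births 3 years before and after" each of them. No conception-based index is mentioned. The Outcomes section defines preterm birth as delivery before 37 weeks and "low birth weight (<2500 g, irrespective of gestational age"; both come from the medical birth register (MBR).

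On timing, the Policy reforms section states that "All reforms were implemented nationally on 1 January of the indicated year". On the behavioural response, the same section reports: "An evaluation of the 1986 expansion revealed that an increased proportion of Swedish-born parents had children in short succession". The Limitations section raises the possibility of the reform "encouraging more parents eligible for earnings based benefits to have children after 1986" and adds: "Parents have been shown to respond quickly to policy changes". It treats this as a question of who has children, to be handled by before/after descriptions, subgroups and sensitivity analyses. The time series models are to allow for seasonality, trend and autocorrelation. Additional analyses adds several intervention points, pseudo-intervention dates and falsification outcomes.

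**The concern.** A preterm birth and a term birth in the same calendar month come from different conception months, the preterm one from the later. The monthly share of preterm births equals the underlying risk only while the number of conceptions is stable. When conceptions rise, the early births of the larger cohorts reach the numerator several weeks before the matching term births reach the denominator, and the share rises for that interval.

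The fertility response that would cause this is also the pathway that RQ#2 studies, so artefact and hypothesised effect would arise at about the same time. Faster second births alone would raise conceptions for a while, even if completed family size did not change. Analyses by nativity could be touched as well: the protocol expects Swedish-born and foreign-born parents to respond differently, so the artefact could differ between the groups and look like effect heterogeneity.

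**Working it through.** The protocol gives no preterm rate, monthly birth count or size of fertility response, so it has no figure of its own to reproduce.

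**Inputs from the protocol:** monthly series, 36 months on each side, reform on 1 January, segmented regression with level and slope terms.

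**Assumptions not in the documents:** constant preterm risk p = 5% (6% gives nearly the same results); preterm births on average 5.4 weeks earlier than term births; conceptions rising by 10% or 20% from the reform date, as a step or a ramp; 2,500 to 8,000 births per month.

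**Formula.** With C(t) conceptions at time t and f(g) the fixed share of pregnancies delivered at gestation g, the birth-time preterm rate is

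R(t) = [sum over g < 37 weeks of f(g)C(t - g)] / [sum over all g of f(g)C(t - g)].

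If C is constant, R = p. Otherwise it is not, although f never changes.

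**Hand checks on size.**

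- *Step, upper limit.* If every preterm birth but no term birth came from the larger cohorts, a 10% step would give 0.05 x 1.1 / (0.05 x 1.1 + 0.95) = 0.0547, or +9.5% relative. Spread over real gestations and grouped by month, the peak is +6.4% (20% step: +12.4%), in month 8. The excess is confined to about months 5 to 9.
- *Step, 36-month mean.* ln(1.1) x 5.4 weeks x 0.95 / 156 weeks = 0.31%, matching the full calculation (0.31%). For 20%: ln(1.2) x 5.4 x 0.95 / 156 = 0.60%, against 0.57%.
- *Ramp.* The excess while the ramp lasts is about (1 - p) x weekly growth x 5.4 weeks. For 20% over 12 months: 0.95 x (0.20/52) x 5.4 = 2.0% (full calculation: peak +1.9%). For 20% over 36 months: 0.95 x (0.20/156) x 5.4 = 0.66% (peak +0.65%).

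**False level change in the segmented regression** (relative, no true effect, approximate):

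| Rise in conceptions | Break at reform | Break at month 9 |
|---|---|---|
| Step, 10% / 20% | +1.1% / +2.1% | -0.9% / -1.9% |
| 12-month ramp, 10% / 20% | +0.6% / +1.2% | +1.0% / +2.0% |
| 24-month ramp, 10% to 20% | +0.2% to +0.5% | +0.6% to +1.2% |
| 36-month ramp, 10% to 20% | +0.1% to +0.2% | +0.3% to +0.6% |

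For a step with the break at month 6 the values are +1.3% and +2.4%. The step values at the reform include two seasonal harmonics; without them they are +0.8% and +1.6%.

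**Standard error.** The relative binomial SE of one month is sqrt[0.95/(0.05n)]. The level change multiplies this by about sqrt(8/36) = 0.471. For n = 2,500: 8.72% x 0.471 = 4.1%. For n = 8,000: 4.87% x 0.471 = 2.3%.

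**Low birth weight.** Assume in addition that 55% of preterm and 1.3% of term births are below 2500 g. The overall rate is 0.05 x 0.55 + 0.95 x 0.013 = 0.0399. A relative preterm excess x moves it by 0.05x(0.55 - 0.013)/0.0399 = 0.67x, about two thirds of the preterm distortion.

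**Planned safeguards.**

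- Seasonality, trend and autocorrelation terms do not describe a shift tied to growth in conceptions.
- Composition checks cannot see it, because it arises with identical composition.
- A pseudo-date without a fertility response would not show it.
- Moving the break changes its size and sign but does not remove it. A larger value at month 6 could be read as a lagged effect.

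**The case against.** The strongest reply is that this is immaterial. Even a 20% step moves the three-year mean by about 0.6%, and for rises up to 20% the false level change is below, or at most about, one SE. A gradual response gives still less. The estimates would also change sign between months 6 and 9 after a step, so the planned set of break points might expose a short transient. All of this stands, and it limits how much weight the point can bear.

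It can also be said that RQ#2 does not state its time index, whereas RQ#4 names the child's month of birth, and that a condensed article may leave the index to a fuller plan. That is fair, but month of birth remains the natural reading of the text, and nothing points to conception month.

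A reader might infer more than the documents support:

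- *That the speed premium is known to raise the number of conceptions.* The protocol reports a higher proportion of Swedish-born parents with short spacing, for the 1986 expansion only. It offers additional births as a possibility, without a size, and reports no measured response for 1980.
- *That the artefact always points towards harm and survives moving the break nine months later.* This holds for ramps; after a step the sign reverses.

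One counterweight remains. A bias is not excused by being smaller than the SE when the estimate is offered as causal. If the reform moved 5 to 10 percentage points of second births into short intervals with 20-40% excess risk (both assumed), the true change in the rate would be only about 0.05 x 0.20 = 1% to 0.10 x 0.40 = 4%. A 1-2% bias is not negligible beside that.

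**Conclusion.** The point holds as a small, avoidable bias. Indexed by month of birth, the preterm series is distorted at constant risk whenever conceptions change, and the low-birth-weight series less so. With a 5% preterm risk and a 10-20% rise, the false level change lies between about -2% and +2% for breaks at the reform or at month 9 (up to +2.4% for a 20% step with the break at month 6). Its sign depends on where the break is placed and how quickly parents respond. The documents do not support the stronger conclusion that this artefact alone would produce an RQ#2 finding: the size of any fertility response is not given, and under the assumed volumes the bias does not exceed about one SE. It deserves correction because the planned checks do not remove it and the remedy is cheap.

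**What to change.** Build the RQ#2 preterm and low-birth-weight series by estimated month of conception, taken as date of birth minus gestational age from the MBR. The outcome is then the proportion of each conception-month cohort born preterm or with low birth weight. Follow every cohort through its last term birth, place the break in conception time, and show the birth-month series alongside. At constant risk the conception-month rate is flat by construction, so this artefact is zero. Changes in who has children still need the checks already planned. At minimum, prespecify the conception-month series as a sensitivity analysis.

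The cost is one derived date and a re-indexed series from data already linked; gestational age is needed for the preterm outcome in any case. Births with missing gestational age cannot be placed, so their number should be reported by period. About 10 more months of births must be read at the end of each window.
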